#### Cost‐effectiveness analysis

5.7.1

An economic evaluation of T‐Control versus the conventional Foley catheter from the public healthcare services perspective will be performed according to the analytical methods accepted by the scientific community.^32^ The cost‐effectiveness measure will be the incremental cost per quality‐adjusted life year (QALY) gained. QALYs are a generic health measure that combines information on life expectancy with the patient's quality of life. QALYs will be calculated based on the health‐related quality of life data collected according to the EQ‐5D‐5L instrument which will be collected for each patient. The time horizon will be the study duration. Costs included in the analysis will be those incurred by the public healthcare service. Unit costs will be obtained from the hospital centres accounting records whenever possible, from the eHealth cost database (Oblikue Consulting), and from national public sources. The mean total cost of each intervention evaluated will be presented using basic descriptive statistics (means, medians, and measures of variability such as variance).

Cost‐effectiveness will be calculated as the incremental cost‐effectiveness ratio which results from dividing the difference in costs between interventions by the difference in effects observed (QALYs). Nonparametric methods based on bootstrapped simulations will be used to calculate the confidence intervals around the incremental cost‐effectiveness ratio. In addition, the same nonparametric methods will be used to construct a cost‐effectiveness acceptability curve that will reveal the probability that each alternative is cost‐effective for different cost‐effectiveness thresholds (willingness to pay for an additional unit of effectiveness). Finally, deterministic sensitivity analysis (one‐way, two‐way, and multiway) will be performed with the aim of analysing the impact of the parameters on the cost‐effectiveness results. The analysis will be performed using the software R and the statistical package STATA (StataCorp LLC, College Station, USA).

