**Patients and Methods:**

Eligible patients are male and female adults aged ≥18 years, who require a change of long‐term bladder catheter. The estimated sample size is 50 patients. Patient follow‐up includes both the time of catheter insertion and its removal or change 4 weeks later, plus the time until the discussion groups take place.

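### Section 5.7.1 plans an unconditional bootstrap confidence interval for the ICER, which cannot be read if the QALY difference is not clearly away from zero

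*Protocol article*

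**What the plan says.** Section 5.7.1 of the protocol article defines the ICER as the result of "dividing the difference in costs between interventions by the difference in effects observed (QALYs"). QALYs come from the EQ-5D-5L, which Table 1 schedules at baseline and 4 weeks only. On the horizon it says: "The time horizon will be the study duration".

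Uncertainty is to be shown in two ways. The first is an interval on the ratio: "Nonparametric methods based on bootstrapped simulations will be used to calculate the confidence intervals around the incremental" cost-effectiveness ratio. The second is an acceptability curve: "the same nonparametric methods will be used to construct a" curve of the probability that each catheter is cost-effective, "for different cost‐effectiveness thresholds (willingness to pay for an additional unit of effectiveness"). Deterministic sensitivity analyses follow.

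The section does not say how the bootstrap interval is formed, what happens if the QALY difference is near zero, or whether incremental QALYs are adjusted for baseline utility. Section 5.7 leaves the detailed analysis to a statistical analysis plan, which is not shown.

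**The concern.** The ICER has the QALY difference as its denominator. If bootstrap replicates of that difference take both signs, the ratios pass through plus and minus infinity, and their numerical order stops matching better and worse. A negative ratio can mean T-Control is cheaper and better (dominant) or dearer and worse (dominated). A positive ratio can mean dearer and better or cheaper and worse. Cut-points taken from the sorted ratios then mark out no coherent range of plausible values.

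Cost-effectiveness is a named secondary endpoint in section 3. An ICER with such an interval could be quoted as the economic result although the interval cannot be interpreted.

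**Working it through.** **Inputs from the protocol article**
- Sample size: "The estimated sample size is 50 patients" (Abstract), allocated 1:1 (section 2.3).
- Section 5.3: significance level 2.5%, standardised difference 0.95, 25 per group, 5% dropout.
- Follow-up: catheter insertion and "its removal or change 4 weeks later" (Abstract).

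**The plan's own figure.** Section 5.3 states no power, so 80% is assumed. A two-sample t calculation (noncentral t) at two-sided 2.5% and d = 0.95 gives 23 per arm. Then 23/0.95 = 24.2, which rounds up to 25. The stated 25 reproduces. Expected completers are 25 × 0.95 = 23.75, so 24 per arm are used below.

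**Further assumptions.** QALY = T × (baseline utility + week-4 utility)/2, with T = 28/365.25 = 0.0767 year. The arms have equal true baseline means. The utility SD is s at both times, with baseline to week-4 correlation ρ between 0.3 and 0.8. The true week-4 difference is d × s.

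**Formulas**
- QALY difference = T × 0.5 × d × s.
- Unadjusted SE = T × s × √((1+ρ)/2) × √(2/n).
- Baseline-adjusted SE = T × 0.5 × s × √(1−ρ²) × √(2/n).

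With s = 0.25, ρ = 0.6 and n = 24:
- Unadjusted SE = 0.0767 × 0.25 × √0.8 × √(2/24) = 0.00495.
- Adjusted SE = 0.0767 × 0.5 × 0.25 × 0.8 × √(2/24) = 0.0022.
- d = 0.95: difference 0.0091. Difference/SE is 0.0091/0.00495 = 1.8 unadjusted and 0.0091/0.0022 = 4.1 adjusted.
- d = 0.5: difference 0.0048. Difference/SE is 0.0048/0.00495 = 1.0 unadjusted and 0.0048/0.0022 = 2.2 adjusted.

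T and s multiply both the difference and its SE, so both cancel from these ratios. The chance of including zero depends on n, d, ρ and how the QALYs are built and adjusted. It does not depend on the length of follow-up.

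**Probability that the two-sided 95% interval for the QALY difference includes zero** (noncentral t, 24 per arm, ρ from 0.3 to 0.8):

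| True week-4 difference | Unadjusted area under the curve | Week-4 utility only | Baseline-adjusted |
|---|---|---|---|
| 0.95 SD | 49% to 60% | 10% | 0% to 8% |
| 0.5 SD | 82% to 86% | 60% | 19% to 57% |
| 0.3 SD | 90% to 92% | 83% | 60% to 81% |
| none | 95% | 95% | 95% |

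**Checks by simulation.** Bootstrapping simulated trials (d = 0.95, ρ = 0.5, unadjusted) gave 53% at a 28-day horizon and 53% at 365 days, which confirms that duration cancels. With d = 0.5, ρ = 0.6, an assumed cost SD of 200 and a cost difference of +30, about 60% of trials had more than 2.5% of replicates in the dominant quadrant and more than 2.5% in the dominated quadrant. That share depends on the assumed costs. If costs clearly differ in one direction, the ratios instead jump between a trade-off and dominance, and the interval is still unreadable.

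**The case against.** Four points can fairly be made for the plan.

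*The acceptability curve already reports uncertainty.* This stands in large part. At each threshold the curve is the share of replicates with positive net benefit, which is well defined whatever the sign of the QALY difference. A reader might infer that cost-effectiveness uncertainty as a whole will be misreported, and the article does not support that. But the curve comes in addition to the ICER interval and does not replace it.

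*The bootstrap rule is not stated.* True: the article does not say that ratios will be sorted for percentiles, and an analysis plan could order replicates by quadrant. The article nevertheless commits to an interval on the ratio scale without condition. When the denominator cannot be told apart from zero, no finite interval on that scale describes the uncertainty properly.

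*The failure is not certain.* This stands. A reader might infer that a trial of this size will usually produce a QALY difference spanning zero. At 0.95, the only effect the protocol states, the probability runs from 0% to 60% depending on how QALYs are built and adjusted. The higher rates mostly need smaller true effects, which are assumptions here. A reader might also blame the four-week horizon. It makes the denominator small in absolute terms (at most 0.077 QALY per patient) and the ICER large, but it does not make zero more likely to be included.

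*Baseline adjustment is a matter for the analysis plan.* This stands. The article is silent on it, so its absence is not an error, and one cannot infer that the comparison will be unadjusted. It belongs here only as part of the remedy.

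**Conclusion.** The point holds in limited form. Section 5.7.1 fixes an ICER interval without qualification, and that interval is uninterpretable whenever bootstrap QALY differences straddle zero to a material degree. With 24 completers per arm this is about an even chance or somewhat more at 0.95 SD, and likely at 0.5 SD, if QALYs are unadjusted areas under the curve. With baseline adjustment it becomes unlikely at 0.95 SD but remains possible at 0.5 SD. These probabilities rest on the assumed correlations, equal true baseline means and effects below 0.95. The assumed SD of 0.25 affects only the SEs on the QALY scale.

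The importance is minor. The study is a pilot, cost-effectiveness is a preliminary secondary endpoint, a valid summary of joint uncertainty is already planned, and neither the primary endpoints nor the sample size is affected.

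**What to change.** In section 5.7.1, or in the analysis plan before data lock:
- Report the ICER as a point estimate, without a confidence interval.
- Give bootstrap intervals for incremental cost, incremental QALYs and incremental net monetary benefit at stated willingness-to-pay thresholds.
- Show the bootstrap replicates on the cost-effectiveness plane, and keep the acceptability curve.
- Estimate incremental QALYs by regression on arm and baseline EQ-5D-5L index. Under the assumptions above (SD 0.25, correlation 0.6) this cuts the SE by a little more than half, and it removes the part of the QALY difference due to chance baseline imbalance.

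The cost is wording only, since the data and software are already planned. The small downside is that thresholds must be named in advance and there is no single ICER interval to quote.

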## DISCUSSION

6

This is the second clinical trial to investigate the new T‐Control catheter in order to provide robustness to the clinical stage of the device and obtain more data regarding it in real clinical practice. As in the first clinical study, one of the most important data to collect is the magnitude and ratio of UTIs developed in comparison with the conventional Foley‐type catheter. However, in this study, the focus is especially on the quality of life of the patients, because eligible participants (men and women) are long‐term catheterized, so this aspect of bladder catheterization has special importance for them. In this regard, the greatest limitation of the study is due to the fact that the instrument developed specifically for the study “Catheter‐related QoL questionnaire” has not yet been validated, and in fact, it is expected to be able to validate it during the course of this study in conjunction with another study specially designed for its validation.

The study could contribute to improving health (infection prevention) and social well‐being (greater quality of life, autonomy, and ability to live with the disease) among patients who use permanent bladder catheters, although it is true that the patients taking part in the study will be men and women with different clinical reasons for being catheterized, which implies a certain degree of heterogeneity in the sample.

It is important to note another of the limitations of the study is although the results analysis team will be blinded by a unique code given to each patient, neither the participants nor the health professionals, the research team involved, and the monitoring team the research team involved and the monitoring team will be blinded. However, the use in the study of both objective and subjective tools to evaluate the different aspects of bladder catheterization related to patients (infections, adverse events, biofilm formation, quality of life, and acceptance of the device), health professionals (burden work and device satisfaction), and impact on the health system (antibiotic treatment prescription and associated costs) is a strength that also should be remarked.

The study aims to promote an active and healthy lifestyle, preventing negative consequences for users. From the point of view of the work environment, the project tries to improve the working conditions of health personnel, reducing occupational risks such as spillage and contamination by contact with urine and offering an easy‐to‐use product that could make it easier to comply with bladder catheter insertion protocols without difficulty or need for additional help.

The development of this clinical study could help the sustainability of the Health System, because it offers a profitable product, with the potential to reduce infections, emergency visits (including the possible need for hospitalization), personnel costs, and so forth. Reducing the need for emergency healthcare visits, with or without admission to hospital care, is of particular interest as the Spanish healthcare system is under severe pressure, partly due to the existing shortage of registered nurses. It also aims to contribute to improving public health conditions, reducing the use of antibiotics, and mitigating the risks of transmission during pandemics such as COVID‐19.

## ETHICS AND DISSEMINATION

7

### Ethics

7.1

This study will be carried out in accordance with the recommendations established in the Declaration of Helsinki and the Standards of Good Clinical Practice. The Hospital Universitario 12 de Octubre Research Ethics Committee approved this study. The taking part of subjects is only contemplated for the current study, so they will not be contacted to offer them the possibility of taking part in subsequent studies. The Ethics Committee, composed of independent members, oversees the trial's conduct and progress. The SPIRIT Statement's recommendations have been followed for the drafting of the protocol and improve their completeness (Data S9).

### Dissemination plans

7.2

A description of this clinical trial is available online (http://reec.aemps.es and https://clinicaltrials.gov/). The full protocol is available at https://clinicaltrials.gov/, and requests for participant‐level data and/or statistical code can be made in writing to [contact]. The final trial data set generated and/or analysed during the current study may be available to the research coordinator and sponsor upon reasonable request.

The findings will be disseminated by means of scientific articles, national and international congresses or meetings, University Associations, both national and international, related to nursing and urology, and internal presentation or promotion for the wider community. The Sponsor adheres to the definition of authorship established by the International Committee of Medical Journal Editors.
